## Abstract

**Background:**

Opioids are frequently prescribed for short-term acute pain following surgery. Used appropriately, opioids deliver extremely favourable pain relief. Used longer than 90-days, however, can result in health complications, including unintentional overdose and addiction. Globally, >40 million people are dependent on opioids and annually >100,000 die from opioid misuse. With >4.7 million surgical procedures occurring annually in the United Kingdom it is imperative that opioid-use is managed upon discharge. A declining General Practitioner (GP) workforce and increased patient numbers, however, means gaps in healthcare during transfer of care. Here we report a mixed-methods protocol to understand the feasibility, and acceptability of a clinical pharmacist (CP)-led early opioid deprescribing intervention for discharged surgical patients.

**Methods:**

DESCALE is a multicentre, non-randomised, pragmatic feasibility study. Participants aged ≥18 years who have undergone a surgical procedure at a single NHS trust in Southeast England and discharged with opioids and without a history of long-term opioid use, cancer diagnosis or study contraindications will be offered a Medicines Use Review (MUR) within 7-10 days of discharge. The MUR will be delivered by CPs at participating GP practices. Feasibility outcomes will focus on recruitment, fidelity of CPs to deliver the MUR, and barriers within primary care that affect delivery of the intervention, with a maximum sample size of 100. Clinical outcomes will focus on the number of participants that reduce or stop opioid use within 91 days. Prescribing, medical, surgical, and demographic data for individual participants will be collected and analysed to inform future trial design. Qualitative interviews with participants and associated healthcare professionals will explore acceptability and implementation of the intervention.

**Conclusion:**

Data collected with respect to opioid use post-surgery, feasibility and acceptability of the intervention, patient experience and outcome data will inform the design of future research and larger clinical trials.

## Introduction

### The opioid problem

Opioids are very strong painkillers that are frequently prescribed to treat short-term acute pain, such as after having a surgical procedure. Used for acute or end of life pain, these drugs deliver favourable analgesic pain-relief. Opioids can however cause serious health risks and side effects such as more pain, medication dependence and in some cases unintentional overdose or premature death from misuse if used for a long period of time (>90-days)
^
1,
2
^. In the United States (US), a White House commissioned report in 2017 into opioid misuse, found that it was responsible for the death of 64,000 people annually and the leading cause of death related to unintentional injury
^
3,
4
^. In the United Kingdom (UK), during the period 2020-2021, almost half (49.6%) of all drug-related deaths involved an opioid
^
5
^. Despite the high potential for serious adverse events when using opioids, the global numbers of people using opioids, over the past two decades has risen dramatically, along with an associated increase in long-term dependency and mortality
^
6–
10
^. In 2017, it was estimated that 40.5 million people were classified as ‘dependent’ on opioids and 109,500 people had died from opioid overdose, worldwide
^
10
^. The first few days of opioid therapy have been shown to be crucial in determining the likelihood of long-term opioid use. Patients receiving opioids for longer than a week, were found to double their risk of using opioids for more than a year, which doubled again if opioids were used for longer than a month
^
11,
12
^. Whilst another study has shown that the cumulative opioid dose dispensed in the first month was also strongly related to the probability of long-term use, with long-acting drugs being worse, than short-acting drugs
^
13
^.

### Surgical opioid use

Opioids are routinely used pre-, intra-, and post-surgically for the treatment of acute pain and post-operatively for pain management and is a primary route to exposure to these types of medicines, often for the first time
^
14,
15
^. Evidence from the US and Canada has shown a clear link between post-surgical opioid prescribing for both minor and major surgery, and persistent long-term use in the community, beyond tissue healing. Inappropriate prescribing of opioids both peri- and post-operatively, accounts for 36.5% of all opioid prescribing in the US, with 3 – 10% of these patients transitioning to long-term use
^
11,
14,
16,
17
^. Patients undergoing surgery are almost four times more likely to be discharged with opioids than their non-surgical counterparts
^
18
^. This is often with more opioid medication than is actually required to treat post-surgical pain
^
19–
22
^. Perhaps more alarmingly, almost half (45%) of these patients are given opioids even though they would not have been taking any opioids at point of discharge
^
23
^. In the United States (US), a study showed that between 5.9 – 6.5% of all patients who underwent surgery (versus 0.4% of the non-surgical control) went on to become long-term opioid dependent, even if they had never taken opioids before
^
15
^.

It is becoming clear from the US, that postsurgical prescribing of opioids is a problematic, underexplored, new source of long-term opioid use
^
17
^. Compared to the US and Canada, less is known in the UK about peri-operative opioid prescribing in hospitals and any link to long-term use. Two recent studies in the UK have identified long-term opioid use (>1 year) to be associated with older age (>75 years), being socioeconomically disadvantaged, having a history of depression and/or alcoholism, prior gapapentinoid or psychotrophic use, and those initiated on >120 morphine milligram equivalents (MME) following major surgery
^
6,
24
^. There are over 5.6 million opioid prescriptions dispensed each year in the UK, corresponding to around 13% of the adult UK population
^
25
^ and over 4.7 million surgical procedures occurring each year
^
26
^ and nearly 8 million people on surgical waiting lists, with over 300,000 waiting more than 52 weeks for surgery
^
27
^. This, along with no current national guidelines on peri-operative opioid prescribing, a declining GP workforce and increasing patient numbers
^
28
^, policy makers and professional bodies are rightly concerned. In 2020, the Faculty of Pain Medicine and Royal College of Anaesthetists established a working party to set out ‘guiding principles’ in opioid management in the peri-operative period
^
29
^. In these guidelines, they acknowledge the critical role that surgery plays in the burgeoning opioid problem: “
*We have a duty to act to minimise the role that anaesthesia, surgery and primary care may have in contributing to the “opioid load” in the community in the UK. It is imperative that all healthcare professionals involved in surgery and perioperative care, work collaboratively to ensure robust opioid stewardship”*
^
29,
30
^. Whilst, the National Health Service (NHS) England Medicines Optimisation Executive Group have made reducing opioid use in chronic non-cancer pain a priority of the integrated care boards for 2023/2024
^
31
^.

### Opioid problem in East Kent

Prescribing of high-dose opioids in East Kent has long been a growing concern within the NHS Kent and Medway Integrated Care Board and Integrated Care System (previously known as the Clinical Commissioning Group (CCG)). A recent report from Public Health England (PHE) highlighted East Kent Health and Care Partnership as being one of the top 30 highest opioid prescribers in England, with an opioid spend of £422,000/year above the national average and prescribing rates 3 – 4 times above the Kent and Medway CCG average
^
25
^. This has led to initiatives such as the East Kent High Dose Opioid Reduction project, a pharmacist-led intervention, established to tackle, high-dose long-term opioid users on >120 mg morphine milligram equivalent (MME) per day
^
32
^. Despite the success of such projects to reduce harmful levels of opioid use in the East Kent community, they do not allow us to understand the root source of the opioid problem from which these complex opioid users arise. Local prescribing and chronic pain clinical leads supporting this study are therefore keen to understand why these patterns of prescribing exist and what preventative opportunities might reduce prescribing and is where our study is based. Deprescribing opioids in a timely manner is important to minimise both the risk of any patient developing opioid tolerance and the possibility of any withdrawal symptoms or adverse events occurring. 

### Pharmacists and opioid management

Pharmacists are experts in medicines management and are trained to deliver high-risk Medicines Use Reviews (MURs), an activity that the public closely associate with the role of a pharmacist
^
33–
35
^. Indeed, in the UK, community pharmacists are contracted as part of the Community Pharmacy Contractual Framework
^
36
^ to deliver MURs to patients and by clinical pharmacists based in GP practices, as part of the additional role reimbursement scheme
^
37
^. However, for community pharmacists, access to a patient’s medical records and GP, can be a limiting factor
^
38
^. particularly when deprescribing medications such as opioids. Thus, clinical pharmacists employed in GP practices with access to patient hospital discharge lists, medical records and onsite support from GPs are ideally positioned to initiate early opioid deprescribing in post-surgical patients discharged back into the community.

### Aims and objectives

The primary aim of this study is to evaluate a multi-centre, pharmacist-led, early opioid deprescribing intervention. This is designed for patients discharged following a surgical procedure with an opioid prescription from hospitals within a single NHS Trust in an area of high opioid prescribing, East Kent. It will determine whether this designed intervention is able to support early deprescribing of opioids in this particular healthcare setting and with this particular patient population and to inform a much larger, clinical trial. A summary of the aims and objectives for this study are collated in
Table 1.

**Table 1. T1:** Summary of study aims and objectives.

Aims/questions	Objectives
**To test the feasibility of delivering an early opioid ** **deprescribing intervention in primary care, led by ** **trained clinical pharmacists.**	**Ascertain stakeholder acceptability of the intervention:** • Maintain detailed records of any barriers or enablers that may occur in response to setting up the intervention and whilst delivering the intervention • Deliver stakeholder interviews
	**Measure the capabilities of trained clinical pharmacists to deliver an ** **early opioid medication review by**: • Completed intervention delivery training • Observational competency checks by Clinical Lead • Completed medication review case reports • Number of participants successfully deescalated
	**Ascertain participant acceptability of the intervention by measuring**: • Number of participants that enrol in the study • Number of withdrawals from the study • Adherence to pharmacist medication recommendations • Responses to participant satisfaction questionnaire • Responses during participant interviews
	**Apply a micro-costing approach to estimate the intervention costs:** • opioid medication costs • staff costs • Health resource use (primary care services, community-based services, hospital inpatient and outpatient services)
**To measure successful discontinuation and/or ** **reduction in the use of opioids to within the ** **recommended 2–4-week period for opioid use ** **or by the expected period of tissue healing (<91 ** **days) whichever is sooner ^ 39 ^.**	**Measurement of** the mean difference in morphine milligram equivalent (MME) dose at baseline and at 90 days
**To understand post-surgical opioid prescribing ** **experiences including opioid use, long-term ** **opioid use, participant pain and quality of ** **life in the 3-month period post-surgery when ** **discharged with an opioid prescription**	• Collect medication use data at baseline and at all follow-up appointments • Compare opioid prescribing (type, dose, amount) at baseline for each surgical speciality and hospital • Measure pain scores at baseline and final visits • Measurement of risk factors in the participant population that have been previously linked to long-term opioid use ○ Baseline demographics; ○ Medical, prescription and surgical histories. • Response to Quality-Of-Life questionnaire (EQ5D-5L) complete at baseline and final appointment • Responses during participant interviews
**To ascertain the feasibility of delivering the ** **intervention as per the protocol to inform a ** **future study or adoption of the protocol**	**Measurements of:** • Time spent finding and recruiting participants • Number of possible surgical participants per week that could receive intervention • Number of pharmacists available to deliver the intervention • Number of surgical participants that accept an early MUR versus the number that are asked • Time taken from hospital discharge to receiving first MUR. • Average time taken for each appointment • Average time taken to successfully deescalate opioids in surgical patients • Number of participants that are successfully deprescribed opioids within 3 months • Number of patients that require additional appointments with the pharmacist • Number of participants that require additional support post-90 days • Responses during participant interviews

## Protocol

### Patient and Public Involvement

The patient and public involvement and engagement team (PPIE) consists of 3 National Institute for Health and Care Research (NIHR) Research Champions from Kent Community Health Foundation National Health Service (NHS) Trust, who have reviewed and modified the protocol and informed the content of the study, to ensure a patient-centred approach. In addition, each Research Champion has undergone qualitative research training, assisted in designing the interview schedule and are involved in delivering qualitative interviews to patient participants of the study. Two members of the public, with experience of receiving post-surgical opioids, participated in practice training MURs with the clinical pharmacists and two additional public contributors joined the research team, participating in monthly project meetings, assisting, and embedding their support in the project as it progresses. On completion of data collection, we will continue to work with the PPIE team to develop lay-friendly summaries of the findings for dissemination to the participants and public.

### Methods

**
*Study design and setting.*
** This is a prospective multi-centre, non-randomised, pragmatic feasibility sub-study, within the larger DESCALE study. The study involves clinical pharmacists based in GP practices in East Kent, initiating an early opioid MUR to support pain management and initiate opioid de-escalation, for surgical patients discharged from a hospital belonging to East Kent Hospitals University NHS Foundation Trust (EKHUFT). The study identifies potential participants from surgical discharge letters by practice staff, before an initial eligibility check, and consent to take part. A baseline MUR is conducted within 7 – 10 days of hospital discharge and continued monitoring and follow up MURs conducted as per the study design (see Study Flow Chart –
Figure 1) until opioids have been discontinued or the participant is 3-months post-discharge
^
39
^. Recruitment of GP sites and participants, commenced in January 2024 and will continue until September 2024. We have currently recruited six primary care GP practices from East Kent to participate in the study.

**Figure 1. f1:**
[figure not shown]
DESCALE Study Flow Chart. Abbreviations: PIL – patient information leaflet; hrs – hours; GP – general practitioner; MUR – medicines use review; EQ5D-5L – European Quality of Life 5 Dimension 5 Level survey. Image created with BioRender.com.

### Trial registration

ClinicalTrials.gov: NCT06396663 (02/05/2024)

Accessed at:
https://clinicaltrials.gov/study/NCT06396663

### Protocol version

Protocol Version 11, approval date 03.05.2024

### Eligibility criteria

**
*Inclusion criteria*
**

Adults aged ≥18 yearsUndergone surgery in a hospital belonging to EKHUFT, who were discharged with opioid medication ≤120 mg MME/day and registered at a participating East Kent, GP practice.

**
*Exclusion criteria*
**

Aged ≤18Unable to provide written informed consentOn a dose of opioids >120 mg MME/dayTaken opioids for >90 days prior to having surgeryTaking opioids for malignant painFollow-on surgery planned in the next 3 monthsUndergone a caesarean sectionPregnantA history of using methadone or injecting opioidsConsidered vulnerable (e.g., severe dementia, severe co-existing or terminal medical condition).

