### Recruitment

**Participants**: Participants identified as having had surgery and discharged with opioids (<120 mg) within the last 7 days via participating GP practice sites undertaking weekly database searches and/or by screening discharge letters will be contacted by either an email or text, inviting them to participate in the study and providing a link to the patient information leaflet (PIL). Invited participants will then be contacted by the practice using a consecutive sampling approach via telephone within 48 hours of the invite being sent, asking if they would like to take part in the study, answering any questions and confirming their eligibility. For patients that agree to participate, an MUR appointment (online, telephone or in person) will be arranged with the pharmacist and a link to an online consent form sent to the participate to complete.

**Sample size:** A sample size of 80 – 100 participants will be recruited. Statistically, sensitivity power analyses have confirmed that the proposed number is able to detect significant differences of the expected effect size and is in line with the recommended sample size of 70 to estimate key parameters, bench-marked from external pilot randomised controlled trials
^
40
^ and will allow for participant loss, to follow-up.

**GP practices:** By utilising networks locally an Expressions of Interest document was circulated to GP practices in Kent. Further to this, research active practices in East Kent and South Kent were approached directly and capacity and capability assessed. Moreover, the project’s Clinical Lead contacted clinical pharmacists who had interest in, or experience in research of opioids or pain, to invite them to express interest in recruiting via their practice(s).

**Clinical pharmacists:** GP practice-based clinical pharmacists with experience of delivering MURs and opioid deprescribing will be recruited from participating practices. The clinical pharmacist/s will receive detailed information about the study, undergo some training with the study Clinical Lead and will be asked to provide written informed consent.

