### Pathway C – Continuation of opioids

In some instances, the clinical pharmacist will recommend that the patient should continue taking their prescribed opioids, which is reviewed again after one week, if:

➢Benefits of taking opioids outweigh the risk of discontinuing opioid therapy➢Prior opioid use was for another condition not related to the surgical procedure➢Patient does not want to discontinue their opioids

Pathway’s will not be exclusive to allow for patient variability in opioid withdrawal coping, and ongoing pain management and thus possible that patients will transition between pathway A and B, and from pathway C to B or A. We anticipate that for most participants, where opioids are being used primarily for the treatment of post-surgical pain or acute injury, pain which should normally subside after 3 – 4 days, and receiving opioids for the first time, will not require complex de-escalation protocols and psychological support. For those participants who have required prior (≤90 days) opioid use to manage their condition prior to surgery, or opioids for an unrelated condition, or on a higher dose, a more gradual discontinuation of opioids or referral to a specialist pain service, may be required.

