### Outcomes measures

The primary outcome of the DESCALE study are to determine the feasibility of the designed intervention to support early deprescribing of opioids in this particular healthcare setting, using this particular healthcare personal and with this particular patient population, in order to inform a much larger, clinical trial. A summary of the study outcomes are listed in
Table 3.

**Table 3. T3:** Summary of outcome measures.

	Outcome Measure(s)
1	**Determination of** the fidelity of an early opioid deprescribing intervention led by trained clinical pharmacists in primary care and their role in the wider medicine’s optimisation programme
2	**Determination of** the barriers/enablers that affect the delivery of the intervention from the perspective of the NHS stakeholders
3	**Determination of** the barriers/enablers that affect the delivery of the intervention from the perspective of the surgical patient
4	**Establishment of** the cost of delivering the intervention from the health/social care provider (NHS), perspective
5	**Determination of** the percentage of participants that reduce or stop opioids within 91 days
6	**An understanding of** trends in surgical opioid prescribing, surgical related pain, and risk factors that contribute to long term opioid use
7	**Determination of** the integrity, robustness, and transferability of the protocol for future adoption by the NHS

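### Patients who stopped opioids before the pharmacist's review can be enrolled, and with discharge as the reference point their stopping can count as success in outcome 5

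*Protocol article*

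**What the plan says.** Under Eligibility criteria, entry rests on the discharge prescription: patients "who were discharged with opioid medication ≤120 mg MME/day and registered at a participating East Kent, GP practice". No exclusion criterion concerns a patient who has since stopped. Under Recruitment, practices find patients by "undertaking weekly database searches and/or by screening discharge letters" and then telephone them, "asking if they would like to take part in the study, answering any questions and confirming their eligibility".

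On timing, Methods states: "A baseline MUR is conducted within 7 – 10 days of hospital discharge". The Pathway C section describes, for most participants, "pain which should normally subside after 3 – 4 days". The introduction (Surgical opioid use) cites literature in which "almost half (45%) of these patients are given opioids even though they would not have been taking any opioids at point of discharge".

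The itemised baseline form (Study MUR and biopsychosocial assessment protocol) lists the opioid and its daily and total quantity as prescribed. Table 1 separately plans to collect medication use data at baseline and at every follow-up.

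Outcome 5 in Table 3 is "the percentage of participants that reduce or stop opioids within 91 days". The reference point for the morphine-equivalent change is baseline in Table 1 and discharge in Statistical analysis. Table 1 also lists, as a feasibility measure, "Number of possible surgical participants per week that could receive intervention".

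**The concern.** The review comes several days after the point at which the article expects pain to have subsided for most participants. Some patients will plausibly have stopped by then, and the written criteria let them in. Pathways A, B and C discontinue, taper or continue an opioid. None is described for someone with nothing left to deprescribe.

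If such a patient is counted as having reduced or stopped within 91 days, the intervention is credited with something that happened before it began. The same applies to the number successfully de-escalated, which Table 1 lists as a measure of pharmacist capability, and to the average time to de-escalation, which would be shortened. The study exists to inform a larger trial. That trial would borrow the success proportion and the weekly yield, and both could err in the favourable direction.

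**Working it through.** **The plan's own figure.** The article gives no success rate or expected share of early stoppers to reproduce. Its one related figure is the sample size of 80–100, tied to a benchmark of 70 plus loss to follow-up. 70/(1−0.125) = 80 and 70/(1−0.30) = 100, so the range fits 12.5% to 30% loss. The sensitivity power analyses cannot be reproduced because the article does not give their inputs. The point does not depend on them.

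**Inputs.** f is the share of participants who stopped before the MUR. p is the proportion who reduce or stop among those still taking an opioid at the MUR. Both are assumptions. The upper value of f, 45%, is the article's cited figure for non-use at discharge; it does not describe this trust at days 7–10. p is varied over 50%, 70% and 90%.

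**Outcome 5 with discharge as reference.** Early stoppers all score, so observed = f + (1−f)p and inflation = f(1−p). For example, f = 0.20 and p = 0.50 give 0.20 + 0.80 × 0.50 = 0.60, which is 10 points too high.

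| f | p = 50% | p = 70% | p = 90% |
|---|---|---|---|
| 10% | 55% (+5) | 73% (+3) | 91% (+1) |
| 20% | 60% (+10) | 76% (+6) | 92% (+2) |
| 30% | 65% (+15) | 79% (+9) | 93% (+3) |
| 45% | 72.5% (+22.5) | 83.5% (+13.5) | 94.5% (+4.5) |

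**Outcome 5 with baseline as reference.** If baseline is the amount actually taken on Day 0, an early stopper starts at zero and cannot reduce or stop. Kept in the denominator, that patient pulls the figure down: observed = (1−f)p, so f = 0.20 and p = 0.50 give 0.80 × 0.50 = 40%. The same patients could therefore produce 60% or 40% depending on which section is followed. If baseline is taken from the prescribed quantity, the early stopper scores as under the discharge reference.

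**Weekly count.** As a count of patients with an opioid left to deprescribe, it is too high by 1/(1−f): 1.11, 1.25, 1.43 and 1.82 for f = 10, 20, 30 and 45%.

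**Participants still using at the MUR, N(1−f), of 80–100.** 72–90, 64–80, 56–70 and 44–55 for the same f. The number falls below 70, before any loss to follow-up, once f exceeds 12.5% (N = 80) or 30% (N = 100).

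**The case against.** - **Status at the MUR may not be lost.** Table 1 plans medication use data at baseline, and Pathways A and B turn in part on how long the patient has been taking opioids, so the pharmacist has reason to ask. This stands: a reader might infer that early stoppers could never be separated afterwards, and the article does not support that. What remains is that the itemised form records prescribed quantities and no stated outcome uses current-use status.
- **Scoring as success is not stated.** De-escalation success is undefined, and no section assigns an already-stopped patient to a pathway or counts that patient. This also stands. The inflation arises with a discharge reference, or if baseline is taken from the prescribed quantity.
- **The weekly count is correct as defined.** The intervention is a review offered to patients discharged with opioids, and someone who has stopped can still receive one. Taking all such patients is a legitimate pragmatic choice. It would be wrong to call this count an error; it only answers a different question from how many have an opioid left to deprescribe.
- **The large figures rest on an unfavourable pair of assumptions.** The introduction cites 3–10% of US surgical patients moving to long-term use. If overall stopping were 90–97%, solving f + (1−f)p for p gives inflation of about 0.8 to 2.5 points at f = 20% and 2.5 to 8.2 at f = 45%. The 95% half-width at 90% with 80–100 participants is 1.96√(0.9 × 0.1/n), about 6 to 7 points. This is fair: the bias could be minor.
- **Other material might contain a check.** Table 2 has eligibility checked twice, and the flow charts and full protocol are not shown. The written criteria being checked, however, contain no current-use condition.

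**Conclusion.** The point holds in a limited form. As written, patients who have already stopped can be enrolled. The article does not show that they are enrolled, or how many. With outcome 5 taken over all participants and change measured from discharge, their stopping can count as success although it preceded the intervention. With change measured from actual use at baseline it would not, so Table 1 and Statistical analysis must be reconciled.

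The inflation is f(1−p): about 1 to 22.5 points over the assumed ranges, and only a few points if most current users succeed. A reader might take 22.5 points as the expected bias. The documents do not support that, because 45% is a literature figure for use at discharge and p = 50% has no source in the article. The weekly count needs a companion figure, not a correction.

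**What to change.** 1. Ask at the eligibility call whether any opioid is still being taken. Record the answer at the baseline MUR with the date last taken, separately from the prescribed quantity.
2. Report the number already stopped before review as a feasibility result.
3. Report outcome 5, the number successfully de-escalated, time to de-escalation and the weekly count among participants taking an opioid at the MUR, with the all-participant figures alongside.
4. State one reference point for change in opioid use, discharge or baseline, and use it in both Table 1 and Statistical analysis.

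Nobody need be excluded, and no dose or clinical rule changes. The cost is one screening question, one case report form item, a smaller denominator and a less favourable percentage. The article reports 18 participants recruited by 23 July 2024, so at that date 62 to 82 of the planned 80–100 could still be captured prospectively. For those already enrolled, status would have to come from the medication use data, if it was recorded.
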